## Abstract

**Background:**

Endovascular repair of aortic aneurysmal disease is established due to perceived advantages in patient survival, reduced postoperative complications, and shorter hospital lengths of stay. High spatial and contrast resolution 3D CT angiography images are used to plan the procedures and inform device selection and manufacture, but in standard care, the surgery is performed using image-guidance from 2D X-ray fluoroscopy with injection of nephrotoxic contrast material to visualise the blood vessels. This study aims to assess the benefit to patients, practitioners, and the health service of a novel image fusion medical device (Cydar EV), which allows this high-resolution 3D information to be available to operators at the time of surgery.

**Methods:**

The trial is a multi-centre, open label, two-armed randomised controlled clinical trial of 340 patient, randomised 1:1 to either standard treatment in endovascular aneurysm repair or treatment using Cydar EV, a CE-marked medical device comprising of cloud computing, augmented intelligence, and computer vision. The primary outcome is procedural time, with secondary outcomes of procedural efficiency, technical effectiveness, patient outcomes, and cost-effectiveness. Patients with a clinical diagnosis of AAA or TAAA suitable for endovascular repair and able to provide written informed consent will be invited to participate.

**Discussion:**

This trial is the first randomised controlled trial evaluating advanced image fusion technology in endovascular aortic surgery and is well placed to evaluate the effect of this technology on patient outcomes and cost to the NHS.

**Trial registration:**

ISRCTN13832085. Dec. 3, 2021

## Administrative information

Note: the numbers in curly brackets in this protocol refer to SPIRIT checklist item numbers. The order of the items has been modified to group similar items (see http://www.equator-network.org/reporting-guidelines/spirit-2013-statement-defining-standard-protocol-items-for-clinical-trials/).

## Introduction

### Background and rationale {6a}

Endovascular aneurysm repair (EVAR) has rapidly replaced open aortic surgery due to perceived advantages in patient survival, reduced postoperative complications, and shorter hospital lengths of stay [1]. Endovascular surgery is planned using 3D reconstructions of pre-operative computed tomography (CT) scans to assess access and determine the optimal type, configuration, and sizing of the implantable medical device. The surgery itself is ‘image-guided’ using 2D X-ray fluoroscopy and injection of nephrotoxic contrast material to visualise blood vessels (see Fig. 1).

**Fig. 1 Fig1:**
[figure not shown]
Graphic showing the 3D information the surgeon has preoperatively, and the intra-operative 2D fluoroscopy in current standard of care endovascular surgery

Despite the potential advantages of EVAR over open surgery, there are significant concerns related to the variability in planning and sizing, high doses of ionising radiation and nephrotoxic contrast material, imprecise visualisation and device positioning, unpredictability of individual patient outcomes, and inconsistent outcomes between hospitals and regions leading to controversy over cost-effectiveness [2, 3]. Device positioning error can require secondary interventions and cause serious and even fatal complications [4].

Previous solutions to improve visualisation during EVAR have included manually aligned, operating table-tracked 3D-2D image overlay. Cydar-EV image fusion is a CE-marked medical device, which instead of a table-tracked overlay uses computer vision to fuse pre-procedural 3D images with intra-operative 2D fluoroscopy automatically and in real-time (see Fig. 2). The key advantage of this type of image fusion is that it gives the surgeon real-time fully integrated 3D visualisation throughout the EVAR procedure with much greater spatial accuracy than achieved by previous technology [5]. The computer vision is a form of artificial intelligence using NHS Digital-approved, GDPR-compliant high-performance cloud computing. Cydar-EV uses only existing patient data (i.e. no new imaging) and is designed not to change clinical workflows. There is no requirement for user interaction, no additional ionising radiation or iodinated contrast. It is agnostic to existing X-ray imaging equipment and can be used on fixed or mobile X-ray systems.

**Fig. 2 Fig2:**
[figure not shown]
Overview of steps in Cydar EV image fusion; pre-procedural 3D images are fused with intra-operative 2D fluoroscopy automatically and in real-time to produce the combined image shown during the surgery

Approximately 5000 EVAR procedures are performed each year in the UK, with an average cost of £19k [6, 7]. EVAR is under an existing NHS care pathway and reduces mortality from 4.7 to 1.7% compared to open surgery, with faster return to normal activities on discharge [1].

Establishing computer vision-powered image fusion as the standard of care in endovascular surgery could directly benefit patients and health and care services by:Reducing procedure times compared to standard procedures and thus improve efficiency of resource use in the NHSReducing patient exposure to anaesthesia and ionising radiation, lowering surgical site infection, and reducing adverse eventsImproving procedural success with more precise device positioning compared to current practiceReducing x-ray exposure to patients and staff and reducing the use of nephrotoxic contrast agent, improving renal functionReducing capital expenditure—Cydar-EV can be easily implemented without the need for linked capital expenditure on new fixed imaging or hybrid operating room (cost to NHS ~£2–5m)

A multi-centre observational study (109 patients) examining safety, performance, usability, and efficacy of Cydar-EV was performed 2014–2015. These data were used in the successful application for CE marking. The primary outcomes were as follows:Robustness: 2802 images were analysed, yielding a positive predictive value of 1, with a lower 95% CI of 0.998.Accuracy: tested against the gold-standard data (Tomazevic 2002), the root-mean-square-error was 0.21 mm (max 0.62 mm) [8].Speed: the mean time taken to return and display an updated 3D overlay in response to patient/table/X-ray set movement was 8.395 s (7.232 s excluding network latency); this has since been significantly reduced to < 4 s.Usability: external usability testing in accordance with IEC 62366 validated the display of the 3D overlay information.

Patient benefit was observed by a significant reduction in the amount of X-rays used, with a mean reduction in X-ray fluoroscopy screening time of 35% (*p* = 0.013), a 41% reduction in the amount of iodinated contrast used (*p* = 0.008), and a nearly 1 h reduction in mean operating time (17%, *p* = 0.06) [9]. A further prospective observational cohort study of 119 patients was conducted at Duke University Medical Centre. This reported a mean reduction in procedure time of 17% (*p* = 0.04), with Cydar-EV and a reduction in the number and duration of unexpectedly very long operations [10]. There was also significantly better renal function after the procedure and at 30 days, an indirect metric of the effect of less nephrotoxic contrast agent, and better device positioning. There are no known additional risks of using Cydar EV in comparison to standard treatment. Interruption of the Internet connection during the procedure is possible but rare (< 0.001%).

Demonstrating Cydar-EV improves the outcomes of endovascular surgery at a lower cost for the NHS would be a key demonstration of the potential of digital technology (cloud-computing, big-data, AI) to improve precision and consistency of outcomes for image-guided surgery. It would establish a new concept of data-guided surgery to deliver intelligent planning and outcome analysis, aggregating and learning from existing data to improve the precision, consistency, and transparency of patient outcomes for stakeholders across the NHS: patients, commissioners, hospitals, and clinical teams.

### Objectives {7}

The overarching aim of this trial is to evaluate the clinical, technical, and cost-effectiveness of a novel type of medical device comprised real-time cloud computing, AI, and computer vision (Cydar EV) compared to standard treatment in endovascular aortic aneurysm repair.

#### Primary objective

The primary objective is to assess the effect of Cydar EV on procedure time in comparison to standard treatment in endovascular aortic aneurysm repair.

#### Secondary objectives

The secondary objectives of this study are to evaluate the following:Procedural efficiency, as assessed by:aAnaesthetic durationbX-ray dose per procedurecContrast dose per proceduredConsumable use per procedureTechnical effectiveness, as assessed by proximal and distal seal zones at least 10 mm and no evidence of endoleakPatient outcomes, as assessed by:aLength of ICU admissionbLength of HDU admissioncPost-operative length of hospital stayd30-day mortalityeRe-intervention—primary hospital visit/further admission (HRG/procedure code)fAdverse events (category, LoS, HDU, ICU, general ward)gQuality of life (EQ5D)Cost-effectiveness, as assessed by:aTotal resource use and costsbQuality-adjusted life years (QALYs)cIncremental cost per QALY

### Trial design {8}

The ARIA trial is a multi-centre, open label, two-armed, parallel groups randomised controlled clinical trial that assigns patients with a clinical diagnosis of abdominal aortic aneurysm and/or thoraco-abdominal aneurysm suitable and fit for endovascular treatment, to either repair using standard treatment or treatment using Cydar-EV. The trial will randomise at a 1:1 ratio and is powered to assess superiority of the intervention. The trial flow diagram is shown in Fig. 3.

**Fig. 3 Fig3:**
[figure not shown]
Flow diagram of ARIA trial design

## Methods: participants, interventions, and outcomes

### Study setting {9}

The trial will be conducted in 10 centres in the UK over 36 months. Three hundred forty patients will be recruited.

Asymptomatic patients will be identified for inclusion at the time of their clinic appointment, while symptomatic or rupture patients will be identified for inclusion at the time of presentation. Patients that present on an urgent or emergency basis will be required to provide written informed consent, after either reading the patient information leaflet or it being read to them by an individual independent of the trial team and the patient’s family.

The expected recruiting sites are as follows:Leeds Teaching Hospitals NHS TrustManchester University NHS Foundation TrustLiverpool University Hospitals NHS TrustUniversity Hospital DerbyNorth Bristol NHS Foundation TrustFrimley Health NHS Foundation TrustImperial Healthcare NHS Trust, LondonGuy’s and St Thomas’ NHS Foundation Trust, LondonUniversity Hospital SouthamptonBrighton and Sussex University Hospitals

### Eligibility criteria {10}

Below are the inclusion and exclusion criteria of the ARIA trial.

Inclusion criteria:Clinical diagnosis of AAA or TAAA suitable for endovascular treatment, as determined by CT imaging and a local treating team multidisciplinary reviewPatient is confirmed fit for endovascular repair as determined by the operating teamCT imaging must be in accordance with Cydar EV: Instructions for UseWritten informed consent (patients lacking capacity or unable to speak English will not be enrolled)Age 18 years and above at the time of consent

Exclusion criteria:Patients unable to provide written informed consent

### Informed consent {26a}

Written informed consent will be obtained by the principal investigator or designee at each site, following explanation of the trial procedures. Discussions about trial participation may take place during an in-person consultation or remotely, i.e. during a telephone or video consultation. The participant information sheet can be sent by post or email ahead of the in-person or remote consultation. Full consent will be given in writing, and the signed original consent forms will be retained on site. Randomisation will only take place once the completed consent form has been received and countersigned.

### Additional consent provisions for collection and use of participant data and biological specimens {26b}

No additional consent will be undertaken as part of this trial.

## Interventions

### Explanation for the choice of comparators {6b}

The control comparator used in the ARIA trial will be endovascular aortic aneurysm repair using X-ray fluoroscopy imaging, which represents the reference standard in England.

### Intervention description {11a}

Patients in the intervention arm of the ARIA trial will undergo endovascular aneurysm repair guided by Cydar-EV. Cydar EV provides tools to:Import and visualise CT dataSegment and annotate vascular anatomy from CT dataPlace and edit virtual guidewires and measure lengths on themMake measurements of anatomical structures on planar sections of the CT dataProduce an operative plan from measurements and segmentation of preoperative vessel anatomyOverlay planning information such as preoperative vessel anatomy onto live fluoroscopic images, aligned based on the position of anatomical features present in bothNon-rigidly transform the visualisation of anatomy when intra-operative vessel deformation is observedPost-operatively review data relating to procedures where the system was used

#### Intervention training

Training on the Cydar-EV product will be as per the Cydar CE marking and Quality Assurance procedures.

#### Intervention delivery

Procedures will be performed under local, regional or general anaesthesia (likely ratio: 1:1:8). Procedures can be undertaken using either a mobile C-arm in a surgical operating theatre, a dedicated fixed fluoroscopy set, or in a hybrid operating room. Patients may go to the ward, HDU, or ICU following the procedure, according to local protocol. Routine pre-operative CT aortic imaging will be used to determine general suitability for endovascular repair, including assessment of landing zones for fixation and sealing, and procedure type and device selection.

### Criteria for discontinuing or modifying allocated interventions {11b}

Cross-over to Cydar EV from standard care will only be permitted in the context of a procedure duration greater than 8 h or where the patient is in extremis and the surgeon believes that using the Cydar technology may be beneficial to complete the procedure. In these circumstances, the Cydar equipment may be used at the discretion of the operating surgeon, and this information must be captured in the reporting system.

### Strategies to improve adherence to interventions {11c}

Reasons for non-compliance could include Cydar EV device failure, Internet failure, surgeon error, failure to communicate correct randomisation allocation to the surgeon, cross-over, and failure to upload images to Cydar EV, or a non-Cydar-trained surgeon performs the procedure. The patient could impact compliance if they express a wish to withdraw between randomisation and surgical procedure or in the event of death.

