### Sample size {14}

There is no known minimum clinically important difference (MCID), and part of the aim of the study is to better characterise the clinical benefit to patients. The study is therefore powered on the basis of a minimum economically meaningful difference. Previous work at Duke [9] reported data on the primary outcome, procedure time, and found a mean difference of 22.5 min (17%) for patients with an abdominal aortic aneurysm treated with Cydar-EV 109.6 (34.2) and standard 2D fluoroscopy imaging 132.1 (69.2) minutes. This is a meaningful difference in the NHS context as this time reduction per case would allow four rather than three EVAR procedures to be performed per day, which is a productivity increase of 33% at the same capacity. The SD for procedure time increases with the mean and so we have assumed a *t*-test for ratio of means 1.2 (fold change), assuming a lognormal distribution for the calculations. Therefore, a sample size of 153 patients per arm with a 1:1 allocation ratio (2 × 153 = 306) would give us 90% power at the 2-sided 5% significance level to detect this difference (PASS 15 Power Analysis and Sample Size Software (2017)). Since our primary outcome measure requires the procedure to be completed, we need to inflate the sample size for possible: (i) loss post randomisation, pre-procedure (est. 7.5%), and (ii) on-table death and cross-overs (where surgeons may use the intervention in a control arm patient and additional assistance is required to complete the operation) (est. 2.5%). These inflate the sample size to 170 per arm. The final randomisation target is therefore 2 × 170 = 340. The Duke data also showed using Cydar-EV in TAAA showed larger reductions in operating time than for AAA. We have powered on the more conservative difference since the relative proportions of AAA/TAAA patients anticipated in our proposed trial is unknown.

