### Implementation {16c}

Patients will be enrolled in the ARIA trial by the local trial team at each of the participating sites as per the described consenting procedure. The allocation sequence generation will be implemented via the Kings College Trial Unit (KCTU) web-based randomisation system. The randomisation of participants will be performed post-consent, after checking their eligibility. The signed consent form will be made available for the operating team to review, along with the randomisation result. Participants will be randomised to Cydar-EV image fusion for guidance or standard imaging techniques in a ratio of 1:1 post-consent and confirmation of eligibility.

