#### CT aorta image reading

CT imaging data will be uploaded to the ARIA trial image analysis virtual CoreLab, which is a cloud-based system. Images will be read in a blinded manner by two readers, with more than 5 years of experience of aortic image analysis and with experience of aortic endovascular surgical planning. They will securely log into the cloud-based Cydar vault where the CT image data will be housed and analyse the pre- and post-operative CTs to determine technical success. Data from this analysis will be entered onto a part of the MACRO EDC system inaccessible to sites. Twenty image data sets will be used to assess the inter- and intra- observer repeatability coefficients for the variables in the CT read protocol.

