#### Statistical methods for primary outcome

As the primary outcome is procedure duration and we envisage 7.5% loss of patients between randomisation and procedure, the primary analysis will be a per-protocol (PP) analysis based on procedure time. The primary analysis will be conducted after completion of first follow-up (at 4–12 weeks) which will include procedure time as well as the secondary outcome data available at this time. Sensitivity analysis with multiple imputation for missing data will also be conducted alongside the per-protocol analysis. No significance tests will be performed for baseline comparison. The primary outcome measure is likely to have a skewed distribution and therefore if necessary and possible the data will be normalised using an appropriate transformation. The data will then be analysed using linear regression techniques with stratification (minimisation) factors included as covariates. If a suitable transformation cannot be found, the data will be analysed using quantile regression to allow us to include the addition of the stratification factors as covariates.

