### Methods in analysis to handle protocol non-adherence and any statistical methods to handle missing data {20c}

Compliance with intervention will be recorded in the source data worksheets and transcribed to the EDC system. Reasons for non-compliance would include device failure, surgeon error, or failure to communicate correct randomisation allocation to the surgeon. The patient could only impact compliance if they express a wish to withdraw between randomisation and surgical procedure. Missingness will be reported and reasons for missingness explored. Although a low percentage of missing data is anticipated, a sensitivity analysis of the primary outcome will be undertaken in order to assess the impact of the exclusion of participants with missing intraoperative data in the primary analysis. In this view of the sample size, a modelling approach will be taken rather than multiple imputation.

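### Failed image upload counts as non-compliance in the Cydar arm only, and a per-protocol primary analysis can then exclude those patients from one arm although their procedure time is known

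*Protocol article*

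**What the plan says.** Four parts of the protocol article bear on this.

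- **Entry.** Eligibility criteria {10} requires every patient's CT to conform to the device's Instructions for Use. Implementation {16c} fixes the order: "The randomisation of participants will be performed post-consent, after checking their eligibility".
- **Non-compliance.** Strategies to improve adherence {11c} gives possible reasons, among them "failure to upload images to Cydar EV". Device failure, Internet failure, cross-over and an operator not trained on the device are listed separately.
- **Primary analysis.** Statistical methods for primary outcome says "the primary analysis will be a per-protocol (PP) analysis based on procedure time". The reason offered is the 7.5% of patients expected to be lost before surgery. The model adjusts for the minimisation factors: surgeon, urgency and procedure type.
- **Sensitivity analyses.** The same section plans multiple imputation for missing data. Section {20c} plans an analysis to "assess the impact of the exclusion of participants with missing intraoperative data in the primary analysis". Neither refers to patients who have a procedure time but did not comply.

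Intention to treat appears in the list of abbreviations, but no as-randomised analysis is described.

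**The concern.** The trial is a superiority comparison of procedure time. The case for a per-protocol analysis is that a patient who never reaches surgery has no procedure time. That does not cover a Cydar-arm patient whose images did not load: the repair can go ahead under standard imaging and its duration can be recorded. Excluding that patient is a choice, made after randomisation, about someone whose outcome is known.

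The exclusion falls on one arm. Control patients are not treated with the device, so a control patient whose images would also have failed to load is never counted as non-compliant and stays in the analysis. If upload failure is related to how long a procedure takes, the comparison is no longer protected by randomisation. Urgent presentations, which leave less time for preparation, are a plausible route, but this is an inference that the protocol does not make.

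**Working it through.** **1. The passages together.** Upload failure is non-compliance {11c}. It concerns delivery of the Cydar intervention, so it arises in one arm. The primary analysis is per protocol. The sensitivity analyses address missing outcomes, and these outcomes are not missing. Hence one-sided exclusion is open, and nothing described would reveal its effect. The per-protocol set is not defined in the article, so exclusion is the natural reading and not a written rule.

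**2. The plan's own sample size.** Sample size {14} says "we have assumed a *t*-test for ratio of means 1.2 (fold change), assuming a lognormal distribution for the calculations", and that 153 per arm "would give us 90% power at the 2-sided 5% significance level to detect this difference". The coefficient of variation (CV) used is not stated. The control-arm figures give:

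- CV = 69.2/132.1 = 0.524
- log SD = √ln(1 + 0.524²) = 0.492
- target = ln(1.2) = 0.1823
- n per arm = 2 × 0.4924² × (1.960 + 1.282)² / 0.1823² = 153.3, so 154 (155 with the exact t distribution)

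With the CV rounded to 0.52 the results are 152 and 153. The stated 153 is reproduced. The allowance is 7.5% + 2.5% = 10%, and 153/0.90 = 170 per arm. That allowance covers loss before surgery, death during the operation and cross-over. Upload failure is not named in it.

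**3. Bias if upload failures are excluded.** The documents give no failure rate and no durations for such patients, so both are assumed. Let a fraction f of the Cydar arm be excluded, with times R-fold those of the patients kept. The Cydar log-mean is then lowered by b = f × ln R. With SE = 0.4924 × √[1/153 + 1/(153(1 − f))], the two-sided type I error is P(|Z + b/SE| > 1.96). For f = 5% and R = 1.5: b = 0.05 × 0.4055 = 0.0203, SE = 0.0570, b/SE = 0.355.

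| f | R | Spurious ratio | b as share of ln(1.2) | Type I error |
|---|---|---|---|---|
| 1% | 1.5 | 1.004 | 2% | 0.051 |
| 2.5% | 1.5 | 1.010 | 6% | 0.054 |
| 5% | 1.2 | 1.009 | 5% | 0.053 |
| 5% | 1.5 | 1.020 | 11% | 0.065 |
| 10% | 1.2 | 1.018 | 10% | 0.062 |
| 10% | 1.5 | 1.041 | 22% | 0.108 |

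With R = 1 there is no bias, and power falls only to 0.883 at f = 10%. With R below 1 the bias has the opposite sign and works against the device. These figures are unadjusted.

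**4. Cost of keeping them as randomised.** If the device has no effect in a fraction f of its arm, the log effect becomes (1 − f) × 0.1823. Power of the t-test at 153 per arm with log SD 0.4924 is:

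| f | Power |
|---|---|
| 0 | 0.898 |
| 2% | 0.886 |
| 5% | 0.866 |
| 10% | 0.828 |

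**The case against.** The article does not say which forms of non-compliance remove a patient from the per-protocol set. Its stated reason for that analysis concerns patients with no procedure at all, and a full definition may stand in a SAP that is not shown. This is fair, and it is why exclusion is called a reading and not a rule. It does not dispose of the point: the article itself fixes per-protocol as primary and itself counts upload failure as non-compliance.

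Urgency, procedure type and surgeon are covariates, so bias that runs through them would be reduced. This stands, and the figures above are on the high side to that extent. The assumed rates and durations have no source in the documents, which also stands. The list of reasons includes cross-over, which can remove control patients, so the net direction across all exclusions is less certain still.

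A reader might infer something stronger: that CT suitability is verified by upload in the Cydar arm alone, after allocation, so that unusable scans are discovered and discarded on one side. The documents do not support this. Conformity is an entry criterion for everyone and eligibility is checked before randomisation. No section makes upload the test of that criterion or says when upload takes place. Upload failure is not equated with an unusable scan and may be purely logistical. Nor are control scans unseen: under CT aorta image reading, the readers work in the Cydar vault and "analyse the pre- and post-operative CTs to determine technical success", with no restriction by arm.

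**Conclusion.** The point holds as one-sided exclusion after randomisation, not as differential testing of eligibility. It rests on two readings: that non-compliance through upload failure leads to removal from the per-protocol set, and that only Cydar-arm patients can incur it.

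Size and direction cannot be derived from the documents. On the assumed values the effect is negligible at 1–2.5% exclusion. It becomes material only near 5–10%, and then only if the excluded procedures are clearly longer (or shorter) than the rest for reasons that the covariates do not capture. There is no error in the sample size arithmetic. The correction is worth making because it is cheap and the patients concerned have the primary outcome recorded.

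**What to change.** In Statistical methods for primary outcome, state that no patient with a recorded procedure time is removed from the primary analysis because of upload failure, and that such patients are analysed in their allocated arm. Keep the per-protocol analysis as a sensitivity analysis.

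No new data are needed. The cost is the dilution in step 4: power goes from about 0.90 to 0.89 at 2% upload failure and 0.87 at 5%, if the device then has no effect in those patients.

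Requiring a successful upload before randomisation in both arms is a less secure alternative. The article does not show that placing a CT in the vault for the blinded read is the same operation as acceptance for image fusion. If emergencies were exempted for lack of time, the patients most likely to be affected would be left out.
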